### Statistical method

Demographic and clinical characteristics of the participating children and parents will be summarized using descriptive statistics. Continuous variables will be presented as means and standard deviations or medians and interquartile ranges, as appropriate, while categorical variables will be presented as frequencies and percentages.

Outcome data will be analyzed at both the individual and group levels. At the individual level, graphical displays will be used to visualize changes over time for each participant across study phases. Visual inspection will focus on changes in level, trend, and variability between baseline and follow-up measurements. These graphical analyses will be used to complement the quantitative analyses and to explore individual response patterns. At the group level, outcome measures obtained at baseline and post-intervention follow-up will be compared using appropriate repeated-measures statistical methods. Depending on the distribution and characteristics of the data, analyses may include paired t-tests or non-parametric alternatives such as the Wilcoxon signed-rank test. Effect sizes (e.g., Cohen’s d or equivalent non-parametric effect size measures) will be calculated and reported to facilitate interpretation of the magnitude of change. Given the limited number of observations within each phase, formal assessment of autocorrelation is not expected to provide reliable estimates. Results will therefore be interpreted with consideration of the dependency inherent in repeated measurements obtained from the same participant and in conjunction with graphical inspection of individual trajectories. In cases where graphical and statistical findings diverge, results will be interpreted cautiously.

Missing data will be described for each outcome measure and study phase. The number and proportion of missing observations will be reported together with reasons for missingness when available. Given the limited number of repeated measurements within each phase, missing values will not be imputed. Analyses will be based on available data, and the potential impact of missing observations on the interpretation of findings will be considered when reporting the results. Participant withdrawal and missed assessments will be reported separately.

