#### Walking, running and Frame Running tests

Three capacity time tests (10-m walk/run, Timed Up and Go, and 30-m Frame Running) will be conducted under standardized and comparable conditions. For children who normally use walking devices or orthoses, the child and parent will select the preferred device together and decide whether orthoses should be worn during testing. All tests will be performed with a stopwatch using the same protocol: three trials will be completed, and if the third trial is the fastest and the child is able to continue, a fourth trial will be added (maximum four trials). All trials will be video recorded to enable subsequent evaluation of gait characteristics such as number of steps, stride pattern, and movement quality. In addition, test conditions—such as the environment, motivational cues, and any unexpected events will be documented to ensure reproducibility across all assessment occasions.

*Time up and go* (TUG) is an observational assessment. TUG measures the time (in seconds) required for an individual to stand up from a standard chair, walk 3 m, turn around, walk back to the chair, and sit down again. In this study, children will start from a height-adjusted stool that allowed sitting position of approximately 90° at the hip and knees. A tape mark on the floor indicates the 3-meter turning point. The test has been widely used in clinical practice as an outcome measure to evaluate functional mobility and dynamic balance [53].

*Time test 10-meter walk/run*, means that the child walks or runs 10 m at their fastest speed.

*Time test 30 m Frame Running* means that the child completes a 30 m straight-line time trial at maximal speed using an individually fitted FR.

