## Discussion

The FSA program aims to address the need for effective interventions targeting gross motor function and health in young children with CP. Currently, there is a lack of evidence for effective training programs for this group of children [11, 64]. In particular, research evaluating interventions for non-ambulant children with CP is scarce; most existing studies have focused on children classified as GMFCS levels I to III, leaving those at levels IV and V underrepresented and often without access to evidence-based interventions [65].

By implementing a new early and intensive program, consisting of a combination of Frame Running and goal-directed training, the FSA program aims to facilitate higher levels of functioning and participation than would be expected without such intervention, both short and long term. If proven effective, this approach could have substantial implications for planning both short- and long-term treatment and support services for young children with CP.

The prospective repeated-measures intervention design allows detailed analysis of individual response patterns over time, while also supporting group-level analyses. This is an advantage, as the variation among children is considerable and prospective repeated-measures intervention design allows for a broad understanding of the intervention impact on each participant, supporting the development of more effective and personalized treatment strategies for children with CP.

This study has limitations. The prospective repeated-measures intervention design does not include randomization or a control group, which limits causal inference. Blinding is also limited, as participants and therapists cannot be blinded to the intervention, although independent assessors will perform outcome assessments whenever possible. In addition, the relatively small sample size and the heterogeneity of children with CP may limit generalizability. Variation in adherence to home-based training may also affect outcomes. However, repeated assessments across study phases and the combination of individual- and group-level analyses are expected to provide important information about the feasibility and potential effects of the intervention.

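### TUG and the 10 m walk/run have no score for a child who tries and cannot finish, and no rule keeps the device constant, so group change may omit some children and partly reflect equipment

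*Protocol article*

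**What the plan says.** The Statistical method section of the protocol article sets one missing-data rule for every outcome: "missing values will not be imputed. Analyses will be based on available data". For the comparison of baseline with follow-up, "analyses may include paired t-tests or non-parametric alternatives such as the Wilcoxon signed-rank test". It also promises that "The number and proportion of missing observations will be reported together with reasons for missingness when available", that the possible impact of missing observations will be considered, and that each child's course will be graphed.

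The section on walking, running and Frame Running tests measures three tests by stopwatch, over three or four trials. TUG requires the child to "stand up from a standard chair, walk 3 m, turn around, walk back to the chair, and sit down again"; the 10 m test is a fastest walk or run. No score or code is given for a child who attempts a test and cannot complete it. The tests "will be conducted under standardized and comparable conditions", but where a child usually relies on a walking aid or on orthoses, the equipment is left open: "the child and parent will select the preferred device together and decide whether orthoses should be worn during testing". Nothing says that this choice, once made, is kept. The test conditions named for recording are examples: "such as the environment, motivational cues, and any unexpected events will be documented to ensure reproducibility across all assessment occasions". Device and orthoses are not among them.

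Table 1 schedules both tests at all six assessments, B1 to F3. Recruitment of participants admits children aged 2–5 years at GMFCS II–IV, and being able to do the timed tests is not an entry criterion. The primary objective concerns mobility with or without assistive devices.

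**The concern.** A time in seconds exists only if the child finishes. For a child who cannot rise, walk 3 m, turn, return and sit, or cannot cover 10 m, the absence of a time is itself information about the outcome. If that child is treated as having a missing value, the available-data rule and a paired test leave the child out. A child who becomes able during the programme, or who loses the ability, would then not enter the group estimate for that test.

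The device question works differently but affects the same two results. The trial aims to change mobility, so some children may change their walking aid during it. A child timed with a walker at baseline and without one at follow-up has done two different tasks, and the second time may be longer although function has improved.

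Both issues fall mainly on the more limited children. The Discussion singles these out: "research evaluating interventions for non-ambulant children with CP is scarce".

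**Working it through.** **Plan's own figure.** Sample size: 3 groups × 6 children = 18, which reproduces. The article states no power, standard deviation or effect size, and no rate of inability or of device change. Everything below is therefore illustration on assumed values, shown over a range.

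**1. How the rules combine.** Times are the only stated result of TUG and the 10 m test; no code exists for inability; missing values are not imputed; the named tests need a value in both phases. A child with no time in the whole of one phase therefore forms no pair. A child with a time at some visits of each phase can still contribute.

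**2. Effect on the 10 m estimate.** Assume that k of 18 children go from unable (scored 0 m/s) to 0.3 m/s, and the other 18 − k gain a mean of 0.05 m/s. Mean over all 18 = [(18 − k) × 0.05 + k × 0.3] / 18.

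| k | Pairs left | Mean, available pairs | Mean, all 18 |
|---|---|---|---|
| 3 | 15 | 0.05 | (0.75 + 0.9)/18 = 0.092 |
| 6 | 12 | 0.05 | (0.60 + 1.8)/18 = 0.133 |
| 9 | 9 | 0.05 | (0.45 + 2.7)/18 = 0.175 |

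Wilcoxon signed-rank power was simulated with 3,000 runs at two-sided 5%, SD of gain 0.15 in the others and 0.05 in the newly able. Available pairs versus all 18 gave 0.21 vs 0.53, 0.16 vs 0.87 and 0.11 vs 0.99 for k = 3, 6 and 9.

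**3. The direction is not fixed.** The table assumes that every child unable at baseline becomes able. With 6 unable at baseline and only j becoming able, the all-18 mean is (12 × 0.05 + j × 0.3)/18: 0.033 for j = 0, 0.050 for j = 1, 0.083 for j = 3. If instead 3 children fall from 0.3 m/s to unable, it is (15 × 0.05 − 3 × 0.3)/18 = −0.008, while available pairs still give 0.05. The omission can hide gains or losses.

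**4. Precision.** The 95% half-width in SDs of change is t(0.975, n − 1)/√n: 2.110/4.243 = 0.497 for n = 18; 2.145/3.873 = 0.554 for 15; 2.201/3.464 = 0.635 for 12; 2.306/3 = 0.769 for 9. The change detectable with 80% power (paired t, two-sided 5%) is 0.70, 0.78, 0.89 and 1.07 SD. This takes the SD as unchanged when the most limited children leave, which need not hold.

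**5. Device change.** Assume 0.6 m/s with a walker and 0.4 m/s without: 10/0.6 = 16.7 s and 10/0.4 = 25.0 s, so a switcher scores 8.3 s worse. If the others each improve by 1.0 s, the mean change with m switchers is [−(18 − m) + 8.33m]/18: −1.0 s for m = 0, −0.48 s for 1, +0.04 s for 2, +0.56 s for 3.

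**The case against.** The strongest reply is that no sentence says such children are dropped. The article is a condensed account, and codes for inability could sit in a test manual, a case report form or an analysis plan that is not shown. The methods are worded openly, so a worst-rank Wilcoxon test is not ruled out. Reasons for missing values will be reported, individual trajectories shown, and statistical results read alongside the graphs. All trials are filmed and follow the same protocol. Testing in the child's current preferred device also fits an objective that includes assistive devices.

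Much of this stands. The exclusion is an inference from two sections read together. A reader might go further and infer that the children who progress most are excluded, or that these results describe only children already walking at baseline. The documents do not support that. They give no count of children unable to do the tests. Devices are allowed, so some children at levels III–IV can be timed. There are three chances per phase to record a time, and a child who loses the ability is left out in the same way as one who gains it.

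What does not stand is that reporting and graphing settle the matter. They describe the loss but leave the group estimate as it is, and a time that does not exist cannot be plotted. Likewise, the promise of comparable conditions does not say that the device is held fixed.

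**Conclusion.** The point holds in limited form. For TUG and the 10 m walk/run, the available-data rule followed as written may leave out children who gain or lose the ability to do the test, and a change in time may partly reflect a change of equipment. The size cannot be derived from the documents. On the assumed values, the 10 m estimate could differ by a factor of about 1.8 (0.092/0.05) to 3.5 (0.175/0.05) if 3 to 9 children all become able, and in the other direction if they stay unable or lose the ability. Two device switchers in 18 could cancel a 1.0 s mean improvement.

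The reach is narrow. Both tests are secondary. The primary GMFM-66 scores each item 0–3, so inability is scored there, and the device choice does not affect it. The 30 m Frame Running test uses an individually fitted frame, so the device question does not arise there either. The change should be made, but the trial's main conclusion does not depend on it.

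**What to change.** **Inability.** Code 'attempted, unable to complete' separately from a test missing for an unrelated reason such as illness or refusal. In the Wilcoxon signed-rank test already named, analyse inability as the worst rank: unable to able ranks as the largest gain, able to unable as the largest loss, and unable in both phases as no change. For the 10 m test, 0 m/s on the speed scale is an alternative; TUG includes rising, turning and sitting, so speed suits it less well. Report the number able at each visit.

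**Device.** Record device and orthoses at every visit. Where feasible, base the paired comparison on trials done in the same device condition at baseline and follow-up; otherwise report results separately for children whose device changed. A rigid rule holding the B1 orthoses for all visits may not be workable over 5–6 months in growing children, so the rule should allow for this. The Functional Mobility Scale already captures a change of usual device as a result in its own right.

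**Cost.** One added code and a device field on the form, a few sentences in the test instructions, a rank-based analysis for these two tests, and a few extra trials for some children. It should be settled before data collection, because the difference between unable and not tested, and the device used, may be hard to recover later.

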### Trial design

The study uses a prospective repeated-measures intervention design with assessments conducted during baseline, intervention, and post-intervention follow-up phases. There will be three baseline measurements, a 12-week intervention phase, and three post-intervention measurements (Fig. 1 and Table 1). Primary clinical outcomes are assessed during the baseline and follow-up phases, while process-related measures, see Table 1. The total study period is approximately 5–6 months.

**Table 1 Tab1:** Assessments to be collected during the training period, B=Baseline, F=Follow up

Assessments	B1	B2	B3	F1	F2	F3
GMFM-66	X	X	X	X	X	X
Funtional Mobility Scale	X	X	X	X	X	X
Time Up and Go	X	X	X	X	X	X
pROM and tonus/MAS		X		X		
Walking/running, 10 m	X	X	X	X	X	X
Frame Running 30 m	X	X	X	X	X	X
Ultra sound	X		X	X		
Gait analysis		X		X		
Pedi-cat, mobility	X	X	X	X	X	X
Prime P/SP	X		X	X		
Accelerometry	X		X	X		X
Goa Attainment Scale			X	X		X
Parent Evaluation						X

This design is informed by principles from single-subject research designs, particularly the use of repeated baseline measurements to characterize within-participant variability before the intervention. However, we do not expect children to return to baseline when the intervention is withdrawn. The planned sample size of at least 18 participants allows also for both individual-level and group-level analyses. This is an advantage when working with heterogeneous populations, such as children with CP, where variability in the magnitude and direction of response to treatment may obscure results in randomized controlled trials (RCTs) [44]. Repeated measurements across phases also allow exploration of individual response patterns and to investigate whether participant characteristics are associated with differential responses to the intervention. Although participants and therapists cannot be blinded to the intervention, outcome assessments are conducted by independent assessors with no involvement in the training phase.

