To ensure for not blinded assessors of GMFM, we have incorporated independent, blinded secondary scoring for a random subset of 20% of the video recordings. Inter-rater reliability (IRR) will be formally assessed using Cohen’s Kappa / ICC. To proactively mitigate bias, if the initial IRR coefficients fall below [e.g., 0.80], a fully blinded primary assessor will be utilized to re-score the entire dataset.

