### Sample size

The group-based intervention will include six children per group, with a total of three groups planned. We aim to include at least 18 children. This sample will allow description of response patterns at the individual level as well as analyses at the group level. Repeated measurements across study phases will make it possible to examine changes over time within participants and across the cohort, thereby strengthening the robustness and generalizability of the conclusions regarding intervention effectiveness.

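### The check on unblinded GMFM scoring uses a pooled agreement coefficient with a placeholder cut-off, and neither is aimed at a scoring shift confined to follow-up

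*Protocol article*

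**What the plan says.** GMFM-66 is the primary outcome (Primary outcome measure). One physiotherapist performs the observational assessments (Procedure for data collection), and the GMFM sessions are video-recorded. The Statistical method section accepts that GMFM assessors are not blinded and describes the remedy:

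- Subset: "we have incorporated independent, blinded secondary scoring for a random subset of 20% of the video recordings".
- Statistic: "Inter-rater reliability (IRR) will be formally assessed using Cohen’s Kappa / ICC".
- Decision rule: "if the initial IRR coefficients fall below [e.g., 0.80], a fully blinded primary assessor will be utilized to re-score the entire dataset".
- Stated purpose: "To proactively mitigate bias".

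Two other places touch on blinding. Trial design says that "outcome assessments are conducted by independent assessors with no involvement in the training phase". The Discussion lists limited blinding as a limitation, "although independent assessors will perform outcome assessments whenever possible".

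**The concern.** The study has no control group, and the group analysis compares baseline with follow-up. An assessor who knows the phase could score follow-up a little higher, and that shift would pass straight into the effect estimate. A useful check has to ask whether the gap between the primary and the blinded score differs by phase.

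A pooled kappa or ICC asks something else: how well two raters agree overall, relative to how much the children differ. With children aged 2–5 years at GMFCS II–IV the differences between children may be large, and they then dominate an ICC. A shift in half of the recordings moves it little.

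The rule is also unfinished. The cut-off is printed as an example in brackets, the coefficient is one of two, and it is not said whether it applies to items or to the total score. This is not detail left to an analysis plan, because the article itself states the decision rule.

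**Working it through.** **No figure to reproduce.** The 0.80 is not derived from anything in the article.

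**Inputs from the article.** "We aim to include at least 18 children"; six GMFM assessments per child (Table 1); 20% scored blind. So 18 × 6 = 108 recordings, and 0.20 × 108 = 21.6, about 22.

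**Assumptions, not in the article.** Between-child SD S = 8–15 points; error SD e = 1.5–2.5 for each rater; occasion SD 1.5; true gain g = 2 points; inflation b added by the primary rater at follow-up only.

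**Step 1: what the ICC responds to.** With half of the recordings from follow-up, the single-measure absolute-agreement ICC is approximately

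ICC = C / (C + e² + b²/4), where C = S² + 1.5² + g(g + b)/4.

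For S = 10, e = 1.5:

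- b = 3: C = 100 + 2.25 + 2.5 = 104.75; ICC = 104.75 / (104.75 + 2.25 + 2.25) = 0.959.
- b = 5: C = 100 + 2.25 + 3.5 = 105.75; ICC = 105.75 / (105.75 + 2.25 + 6.25) = 0.926.

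The ICC reaches 0.80 when b² = C − 4e². At S = 10 and e = 1.5 this is b² = 103.25 + 0.5b − 9, so b is about 10 points. At S = 8 the same equation gives about 7.9.

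**Step 2: how often the rule fires.** Simulation of 22 recordings drawn at random from the 108 (5,000 runs per row, absolute-agreement ICC on the total score). Means lie slightly below the formula because the sample is small. Repeat runs move the percentages by at most one or two points.

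| S | e | b | mean ICC | P(ICC < 0.80) |
|---|---|---|---|---|
| 10 | 1.5 | 0 / 3 / 5 | 0.974 / 0.949 / 0.911 | 0.0% / 0.1% / 2.4% |
| 10 | 2.5 | 0 / 3 / 5 | 0.929 / 0.909 / 0.874 | 1.3% / 3.5% / 10.6% |
| 15 | 1.5 | 0 / 3 / 5 | 0.988 / 0.976 / 0.955 | 0.0% / 0.0% / 0.1% |
| 15 | 2.5 | 0 / 3 / 5 | 0.966 / 0.955 / 0.936 | 0.1% / 0.1% / 0.5% |
| 8 | 1.5 | 0 / 3 / 5 | 0.960 / 0.925 / 0.872 | 0.0% / 1.2% / 10.8% |
| 8 | 2.5 | 0 / 3 / 5 | 0.897 / 0.869 / 0.822 | 5.8% / 12.7% / 31.9% |

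A consistency ICC fires less often still (S = 10, b = 5: 0.2% to 4.4%).

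**Step 3: what that inflation does to the result.** Take no true change, an SD of individual change of 2 (assumed), and a paired t-test on each child's mean of three baseline and three follow-up scores. Then SE = √[(2(e² + 1.5²)/3 + 2²)/18], which is 0.62 at e = 1.5 and 0.73 at e = 2.5. The chance of a false significant gain is 73–86% at b = 2 and 97–99% at b = 3.

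**Step 4: a contrast aimed at the threat.** Let d be primary minus blinded score in one recording. Compare mean d at follow-up with mean d at baseline, 11 recordings each: SE = SD(d) × √(2/11).

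- SD(d) = 2: SE = 0.85, 95% half-width 2.086 × 0.85 = 1.8.
- SD(d) = 1.5√2 = 2.12: SE = 0.90, half-width 1.9.
- SD(d) = 2.5√2 = 3.54: SE = 1.51, half-width 3.1.

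In simulation, the rule that the 95% CI excludes zero fires in about 5% of runs with no bias. At 3 points it fires in about 88–90% (e = 1.5) or 45–49% (e = 2.5). At 5 points it fires in over 99% or about 88%. These rates do not depend on S.

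**The case against.** A reader might infer that the rule cannot detect inflated follow-up scores and would almost never fire. The article does not support that as a general statement, for four reasons.

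- It gives neither the GMFM-66 spread nor the rater error. An absolute-agreement ICC does fall with bias, and at SD 8 with 5 points of inflation the rule fires in about 11–33% of runs.
- Kappa is not out of place in itself. GMFM items are scored 0–3, and kappa can be used on items. In simulation with 10% random item error per rater, unweighted item kappa fell below 0.80 in 2% of runs with no inflation and in 83% with 10% of follow-up items inflated. But with 15% random error it always fell below 0.80, bias or not, and quadratic-weighted kappa never did. The result turns on choices that the article leaves open.
- It is tempting to object that a simple random 20% seldom catches both phases of the same child. That objection fails. Primary minus blinded is a difference within one recording, so the child's level cancels, and different children can serve in each phase. Only balance between phases matters.
- The statements on blinding are compatible. Being independent of the training is not being blinded to phase, and the Discussion admits limited blinding. Aligning the wording is editorial.

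What remains is that the statistic is not matched to its stated purpose. Where it does fire at a narrow spread, part of the firing comes from random disagreement.

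**Conclusion.** The point holds in this form: the rule has an unfilled cut-off on an unchosen coefficient, and a pooled coefficient is not aimed at a shift confined to follow-up. This much is on the page and needs no assumption.

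The size rests on assumed SDs. With a spread of 10–15 points, a 3–5 point follow-up shift would usually pass the check, although 3 points could by itself produce a significant pre-post change. With a spread near 8 the check is less blind but also not specific to bias. The article does not show that such inflation will occur; the weakness lies in the safeguard. It matters because this is the only blinded check described for the primary outcome of an uncontrolled study.

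**What to change.** Keep the 20% workload and change what is drawn and what is judged:

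1. Stratify the blinded subset by phase: about 11 baseline and 11 follow-up recordings, scored in random order with the phase masked.
2. Base the decision on mean primary-minus-blinded difference at follow-up minus that at baseline, with its 95% CI.
3. Pre-specify a trigger that suits this precision, for example that the CI excludes zero. A fixed 1-point trigger would be too tight: at SE 0.85 it is exceeded in either direction in about 24% of trials with no bias, since 2 × [1 − Φ(1/0.85)] = 0.24.
4. When the trigger is met, re-score all recordings blinded and state that the blinded scores become the primary data.
5. Report a named ICC form for the total score, or weighted kappa for items, as description only, and remove the bracketed placeholder.
6. Say the same in Trial design, Statistical method and Discussion: independent of the training, not blinded to phase.

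The cost is wording and a different sampling list, with the same number of videos in the first step and no extra scorer. The downside is that the full re-scoring already foreseen becomes somewhat more likely. The check also remains coarse if rater error is large (half-width about 3.1 points at error SD 2.5). Scoring all 108 recordings blind from the start would need no trigger, at the price of more scoring time.
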